## Introduction

1

Patients diagnosed with fatal cancer have a greater risk of developing anxiety than the general population.^[1]^ In patients referred for surgery, the most common factors contributing to anxiety are concern about family and fear of complications, results of the operation, and postoperative pain.^[2]^ Preoperative anxiety is associated with increased anesthetic requirements,^[3]^ increased pain,^[4]^ nausea and vomiting,^[5]^ and prolonged hospitalization^[6]^ in the postoperative period. Previous articles have reported that 34% of patients with esophageal cancer have possible or probable anxiety prior to surgery,^[7]^ and 16% to 34% of postoperative patients still have anxiety during the follow-up year after diagnosis.^[8]^ Anxiety is a clinical issue in the perioperative period.

Esophagectomy is a standard surgical procedure for the treatment of esophageal cancer. Its morbidity and mortality rates after surgery have decreased in recent decades, but remain higher than those of other thoracic surgical procedures.^[9]^ In particular, postoperative pneumonia is one of the most common and fatal complications after surgery, occurring in 9% to 19% of patients even in recent reports,^[10–13]^ and is a major risk factor of hospital mortality. In a videofluoroscopic swallowing study, 32% of postoperative esophageal cancer patients showed evidence of subglottic aspiration, which is an important preliminary risk of aspiration pneumonia.^[14]^ As such, prevention of postoperative pneumonia is a clinical issue in esophageal cancer surgery.

Together with Western medicine, traditional Japanese (Kampo) medicine has been widely used in Japan for the treatment of both mental and physical disorders. Bukuryoingohangekobokuto (BRIHK) is used for patients with anxiety, depressed feelings, the feeling of a foreign body in the throat and esophagus, nausea, heartburn, nervous gastritis, water brash, and more.^[15]^ Hangekobokuto, which is included in BRIHK, has been reported to improve the impaired swallowing reflex^[16]^ and reduce the risk of pneumonia and pneumonia-related mortality in clinical trials of elderly patients.^[17]^ A recent trial showed hangekobokuto prevented aspiration pneumonia in patients undergoing cardiovascular surgery.^[18]^

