#### Inclusion criteria

2.2.1

1.Scheduled to undergo elective radical resection surgery for esophageal cancer in the upper, middle, or lower parts2.Pre-treatment clinical stage II, III, or IVa according to the 8^th^ edition of the Union for International Cancer Control TNM classification (except for T4b and N3)^[19]^3.Eastern Cooperative Oncology Group performance status of 0, 1, or 24.Hospital Anxiety and Depression Scale (HADS) score ≥ 8^[20]^5.Aged ≥ 20 years at the time of consent6.Either sex7.Provision of written informed consent

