### Interventions

2.3

In study arm P (placebo group), 2.5 g of lactose powder (Pfizer Japan Inc, Tokyo, Japan) will be orally administered 3 times daily before meals from 14 days before surgery to 42 days after surgery. On the day of the operation, administration will be stopped. During the fasting period after surgery, lactose will be dissolved in warm water and administered through an intestinal tube via the transintestinal fistula. Lactate is set as a non-active ingredient.

In study arm A (BRIHK group), 2.5 g of BRIHK will be orally administered 3-times daily before meals on the same schedule and using the same methods as in arm P. BRIHK is a multicomponent formula, originally extracted from 9 crude drugs as follows: 6 g Japanese Pharmacopoeia (JP) Pinellia tuber, 5 g JP Poria sclerotium, 4 g Atractylodes lancea rhizome, 3 g JP Magnolia bark, 3 g JP Citrus unshiu peel, 3 g JP Ginseng, 2 g JP Perilla herb, 1.5 g JP Immature orange, and 1.0 g JP Ginger (JP: the 17th Japanese Pharmacopoeia^[21]^). It is currently prepared for prescription use in Japan as granules through the process of decoction, concentration, drying, and the addition of excipients (Tsumura BRIHK extract granules for ethical use, Tsumura & Co., Tokyo, Japan).^[15]^

We will place a label on both the packages of lactose and BRIHK for blinding. We will monitor the participants’ adherence by having them return unused medication.

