### Outcomes

2.4

The primary outcome measures include mental status and water brash before and after surgery. Mental status will be assessed using HADS, which contains both anxiety and depression subscale scores.^[15]^ Water brash will be assessed using the 10-item Eating Assessment Tool (EAT-10), Esophagus and Stomach Surgery Symptom Scale (ES4) and videofluoroscopy swallowing measurement. EAT-10 is a screening assessment scale for dysphagia.^[22]^ ES4 measures the postoperative symptoms of esophagogastric cancer.^[23]^

Secondary outcome measures include the incidence of aspiration pneumonia, number of postoperative hospitalization days, abdominal gas volume, plasma inflammatory markers, chest computed tomography findings, nutritional status, and laboratory examination findings. Aspiration pneumonia will be diagnosed based on the clinical practice guideline for pneumonia.^[24]^ Abdominal gas volume will be measured by analyzing an abdominal radiograph using Koide methods with Image J.^[25,26]^ White blood cell count, serum interleukin-6, tumor necrosis factor α, and granulocyte-colony stimulating factor will be measured as inflammatory markers. Serum albumin, prealbumin, total cholesterol, retinol-binding protein, transferrin, C-reactive protein, and lymphocytes will be measured as nutrition status markers. We will also evaluate body weight, body mass index, triceps skinfolds, and arm muscle circumference measured using bioelectrical impedance analysis (InBody 770, InBody, Soul, Korea).

Secondary safety measurements will include adverse events, side effects of BRIHK, and laboratory data abnormalities exceeding postoperative change. BRIHK has a possible side effect of hypersensitivity (e.g., rash or urticaria).^[15]^ We will routinely examine the laboratory data for postoperative adverse events such as those involving liver function, kidney function, electrolytes, creatine phosphokinase, glucose, and brain natriuretic peptide.

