### Statistical methods

2.11

The primary statistical analyses will be performed by WDB Clinical Research Co., Ltd. using the full analysis data set, from which patients who withdraw consent before assessment of the primary endpoint will be excluded. In addition, we will repeat the analyses in the per-protocol set, which will exclude patients with major protocol deviation. The safety analysis will be performed using the complete data set in the BRIHK group.

For baseline characteristics variables, summary statistics will be calculated using frequencies and proportions for categorical data; means, standard deviations, medians, and quartiles will be used for continuous values. Patient characteristics will be compared using the Chi-squared test or Fisher exact test for categorical valuables and the Wilcoxon rank-sum test for continuous valuables. For the primary intra-group analysis, we will calculate mean HADS and ES-4 scores for each timepoint with 95% confidential intervals and compare the HADS and ES-4 scores at the baseline with those during the treatment period using Wilcoxon signed-rank test. For the inter-group analysis, we will calculate the change in the HADS and ES-4 scores from the pre- to post-treatment period and compare them between the 2 groups using Wilcoxon signed rank test. Then, we will perform an analysis of covariance with the covariates of patient characteristics and calculate the confidence interval. For the analyses of secondary outcome measures between the 2 groups, we will perform the Chi-squared test or Fisher exact test for categorical valuables and Wilcoxon rank-sum test for continuous valuables. *P* values less than 5% will be considered statistically significant, and we will not adjust *P* values in multiple comparisons.

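### The label *primary* sits on a within-arm before/after test of HADS and ES-4, and the between-arm comparison is not designated as the confirmatory analysis

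*Protocol article*

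**What the plan says.** The protocol's Statistical methods section opens the efficacy analysis with: "For the primary intra-group analysis, we will calculate mean HADS and ES-4 scores for each timepoint". Within each arm it will then "compare the HADS and ES-4 scores at the baseline with those during the treatment period using Wilcoxon signed-rank test". P values below 5% count as significant, without adjustment for multiple comparisons.

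The comparison of arms comes next and is not called primary. Changes in HADS and ES-4 are calculated, and the plan is to "compare them between the 2 groups using Wilcoxon signed rank test". After that: "Then, we will perform an analysis of covariance with the covariates of patient characteristics and calculate the confidence interval". Only then does the section turn to secondary outcomes.

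Three other sections bear on what a within-arm change would mean:

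- Inclusion criteria: "Hospital Anxiety and Depression Scale (HADS) score ≥ 8". The criterion does not say whether this is the total or a subscale score.
- Interventions: treatment runs "from 14 days before surgery to 42 days after surgery".
- Outcomes: "ES4 measures the postoperative symptoms of esophagogastric cancer".

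The Abstract gives the aim as efficacy and safety of BRIHK compared with placebo.

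**The concern.** The trial asks whether BRIHK does better than placebo. A signed-rank test within one arm asks whether that arm changed, and makes no use of randomisation. Two sources of change are shared by both arms:

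- **Perioperative course, both scales.** With treatment starting two weeks before surgery, a pre-treatment baseline precedes the operation and the treatment period spans it. For ES-4, a scale of postoperative symptoms, the before/after difference then includes the effect of the esophagectomy.
- **Regression to the mean, HADS only.** Patients enter because HADS is high. If that entry score is also the baseline, scores tend to fall on re-measurement in either arm. ES-4 is not an entry criterion, so this does not apply to it.

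A significant result from the test labelled primary could therefore arise with no drug effect. If the report treats that test as the main result, a change that the placebo arm shares could be credited to BRIHK or blamed on it.

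**Working it through.** There is no power calculation to reproduce: the Sample size section sets the number by feasibility. Twenty-four patients at 1:1 gives 24 / 2 = 12 per arm.

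**Inputs from the protocol.** 12 per arm; 5% level; entry at HADS of 8 or more; and, from the Introduction, "34% of patients with esophageal cancer have possible or probable anxiety prior to surgery".

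**Assumptions not in the protocol.** Two-sided test; score SD 4 on a 0–21 scale; correlation ρ between baseline and follow-up from 0.3 to 0.9; the 34% taken as the fraction passing the entry cut-off, with 70% as an alternative (for instance if the cut-off applies to the total score). No drug effect anywhere.

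**Step 1: expected fall in HADS.** If a fraction p is selected from the top of a normal distribution, the selected patients lie on average φ(z)/p SDs above the population mean, where z is the (1 − p) quantile. For p = 0.34, z = 0.412 and φ(z)/p = 1.078, so the excess is 1.078 × 4 = 4.31 points. The expected fall on re-measurement is (1 − ρ) × 4.31.

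**Step 2: how often the within-arm test is significant.** Simulation with 2,000 runs per scenario, integer scores, signed-rank test, 12 patients:

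| ρ | Fall by formula | Simulated fall (34% selected) | Significant, 34% selected | Significant, 70% selected | Significant, 34% selected, baseline re-measured after screening |
|---|---|---|---|---|---|
| 0.3 | 3.02 | 3.00 | 64.5% | 16.4% | 4.4% |
| 0.5 | 2.16 | 2.17 | 46.5% | 13.0% | 4.8% |
| 0.6 | 1.72 | 1.74 | 38.6% | 10.1% | 5.1% |
| 0.7 | 1.29 | 1.33 | 29.2% | 8.1% | 4.3% |
| 0.8 | 0.86 | 0.89 | 20.3% | 6.6% | 5.1% |
| 0.9 | 0.43 | 0.44 | 11.7% | 6.1% | 4.4% |

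The middle two percentage columns from the left use the entry score as baseline. The simulation error near 5% is about √(0.05 × 0.95 / 2000) = 0.5 percentage points.

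**Step 3: add a surgery effect common to both arms** (HADS, 34% selected, ρ 0.5 and 0.7):

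- Shift of −0.5 SD (anxiety eases): significant in 94% at both correlations.
- Shift of +0.25 SD: 16.5% and 6.7%. Shift of +0.5 SD: 4.5% and 9.7%. Regression to the mean is largely cancelled.
- Shift of +1 SD: 35% and 80%, as worsening.

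**Step 4: ES-4, no selection, surgery effect only** (ρ 0.5 and 0.7):

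- No shift: 4.2% and 3.8%.
- 0.5 SD: 33% and 48%.
- 0.8 SD: 68% and 88%.
- 1.0 SD: 86% and 97%.

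**Step 5: the randomised contrast on the same data.** A rank-sum test of change between arms was significant in 3.4% to 5.4% of runs across all these scenarios. Its limit is power. By the normal approximation, 12 per arm gives about 23% power for a standardised difference of 0.5 and 50% for 0.8; 80% power needs (1.960 + 0.842) × √(2/12) = 1.14.

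**The case against.** The strongest reply is that *primary* may mean *of the primary outcomes*. The section moves from the intra-group analysis to the inter-group analysis to the secondary outcomes, and HADS and ES-4 belong to the primary outcomes in both of the first two. The randomised contrast is also already planned, with an ANCOVA and confidence interval, in a trial described throughout as randomised and controlled. This stands as a fair reading. It does not settle the matter, because the confirmatory test is then still not named and the within-arm tests keep their 5% threshold.

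A reader might infer that significant within-arm change is to be expected. The figures do not support that for regression to the mean alone: with 34% selected, the rate is below 50% for every ρ of 0.5 or more; it is at most about 16% with 70% selected and about 5% if baseline is re-measured. The schedule figure is not shown, so neither the use of the entry score as baseline nor the pre-surgery timing is confirmed; the timing is inferred from the Interventions section. The documents give no SD, correlation, or size or direction of a surgery effect.

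A reader might also infer that efficacy will be claimed from within-arm significance, or from significance in one arm and not the other. No section sets such a rule.

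**Conclusion.** The point holds as a fault of designation. The only HADS and ES-4 analysis carrying the label *primary* cannot separate a BRIHK effect from change common to both arms, and the analysis that can is not designated as confirmatory.

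The size is uncertain. From regression to the mean alone, the range of roughly 5% to 65% rests on the assumed SD, correlation, selected fraction and choice of baseline, and concerns HADS only. For ES-4 the argument rests wholly on an unquantified surgery effect. The structural point needs none of these assumptions: any shared perioperative change can make the labelled test significant, while the between-arm test keeps its level. The low power of the between-arm test at 12 per arm makes it more important to settle in advance which result counts.

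**What to change.** In Statistical methods:

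1. Designate the comparison of arm A with arm P as the primary analysis of the primary outcomes.
2. Specify it as an ANCOVA with the baseline score among the covariates, or as a Wilcoxon rank-sum test on change. Replace the signed rank test now named for the inter-group comparison: it is a paired test and does not fit two independent arms. The same section already uses rank-sum for continuous secondary outcomes.
3. Present within-arm means with 95% confidence intervals, and any within-arm tests that are kept, as descriptive only.
4. State that no efficacy claim rests on within-arm change.

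The cost is wording in the protocol and analysis plan, settled before outcomes are compared by arm. No extra patients, visits or measurements are needed. The change does not improve power, so the confidence interval for the between-arm difference should be read with the feasibility-based sample size in mind.

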### Study design and setting

2.1

The study will be a single-center, single blind, parallel randomized controlled trial to assess the efficacy and safety of BRIHK for anxiety and postoperative water brash in esophageal cancer patients. Participants will be blind to the treatment assignment throughout the trial. The study design is shown in Figure 1.

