#### Exclusion criteria

2.2.2

1.History of abdominal surgery (except for appendectomy or caesarean section) or ileus2.Inflammatory bowel diseases3.Undergoing emergent surgery for esophageal cancer4.Concomitant use of prohibited medicine 4 weeks before inclusion5.Past history of radiotherapy or chemotherapy for esophageal cancer6.Allergy to Kampo formulas or intolerance to lactose (major excipients of Kampo formulas)7.Severe liver, kidney, cardiovascular, blood, or metabolic diseases8.Pregnant, within 28 days after childbirth, or breastfeeding9.Dementia10.Difficulty with study participation as judged by the researchers

Prohibited medicines in this study include Kampo formulas other than BRIHK and psychotropic agents. Temporary use of hypnotics will be allowed if needed.

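### ES4, described as a postoperative symptom scale, is analysed through a baseline taken before esophagectomy: adjust for that baseline, and do not treat the within-arm test as primary

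*Protocol article*

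**What the plan says.** Study design and setting (2.1) gives the purpose as "to assess the efficacy and safety of BRIHK for anxiety and postoperative water brash in esophageal cancer patients". Outcomes (2.4) lists three instruments for water brash: "Water brash will be assessed using the 10-item Eating Assessment Tool (EAT-10), Esophagus and Stomach Surgery Symptom Scale (ES4) and videofluoroscopy swallowing measurement". It then describes one of them: "ES4 measures the postoperative symptoms of esophagogastric cancer". The same section plans assessment on both sides of the operation: "The primary outcome measures include mental status and water brash before and after surgery".

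Interventions (2.3) sets dosing "from 14 days before surgery to 42 days after surgery", so any pre-treatment score is also a pre-surgery score.

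Statistical methods (2.11) uses that score twice for ES4:

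- Within each arm, a signed-rank test compares baseline with the treatment period. The section labels this the primary intra-group analysis.
- Between arms, "we will calculate the change in the HADS and ES-4 scores from the pre- to post-treatment period and compare them between the 2 groups".

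An analysis of covariance on patient characteristics follows. Baseline ES4 is not named among its covariates. EAT-10 and videofluoroscopy are primary measures in 2.4, but 2.11 names only HADS and ES4 in the primary analyses.

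**The concern.** The article does not say what a scale it characterises as postoperative measures before the operation, yet both ES4 analyses rest on that preoperative reading. Two consequences follow, and they differ in kind.

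- **Between arms.** Subtracting a baseline that predicts the later score poorly adds variance. With 24 patients and a sample size set by feasibility, there is little precision to spare.
- **Within arms.** A major operation lies between baseline and every postoperative score. A significant before/after difference may reflect surgery and time alone, and a drug benefit could be hidden by surgical worsening. Calling this comparison primary invites a reading that it cannot support.

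Because ES4 is the only water-brash instrument named in the primary analyses of 2.11, this affects half of the trial's stated question.

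**Working it through.** **Inputs from the article.** There are 24 patients randomised 1:1, so 12 per arm. The significance level is 5% without multiplicity adjustment; two-sided is assumed. No effect size, SD, correlation or power is given, so there is no planned figure to reproduce.

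**Assumptions.** The pre/post correlation ρ runs from 0 to 0.7. The preoperative SD is k times the postoperative SD, with k = 1 or 0.5. Effects are in postoperative SD units. A two-sample t test (noncentral t, 22 degrees of freedom) stands in for a rank test of two independent groups.

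**Variance relative to the unadjusted postoperative score**

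- Change: 1 + k² − 2ρk, which is 2(1 − ρ) when k = 1.
- Postoperative score adjusted for preoperative score: 1 − ρ².

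**Unadjusted postoperative score.** The effect detectable with 80% power is 1.20 SD. Power at 1 SD is 65%, whatever ρ is. For change, the detectable effect is 1.20 × √(variance ratio), computed before rounding the 1.20.

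| ρ (k = 1) | Variance ratio, change | Detectable effect, change | Power at 1 SD, change | Power, unadjusted postoperative | Power, adjusted postoperative |
|---|---|---|---|---|---|
| 0 | 2.0 | 1.69 SD | 38% | 65% | 65% |
| 0.3 | 1.4 | 1.42 SD | 51% | 65% | 69% |
| 0.5 | 1.0 | 1.20 SD | 65% | 65% | 77% |
| 0.7 | 0.6 | 0.93 SD | 86% | 65% | 91% |

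**Allowance for the covariate.** The adjusted column ignores the cost of estimating the slope. That cost is one degree of freedom (22 to 21) and an expected variance inflation of 1 + 1/20 = 1.05 from chance baseline imbalance. With both included, adjusted power is 63%, 67%, 75% and 89%, still above change in every row.

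**Half the preoperative SD (k = 0.5).** The variance ratio for change is 1.25 − ρ. At ρ = 0 it is 1.25 (power 55%), and at ρ = 0.2 it is 1.05 (power 63%). Change breaks even with the unadjusted postoperative score at ρ = 0.25. At ρ = 0.5, change and adjusted score have the same variance, 0.75 (power 77% each, or 75% for the adjusted score with the allowance). So the adjusted analysis is about level with change at worst.

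**Check on bias.** In a simulation with rank-sum tests (4,000 runs, 12 per arm, both arms shifted by +1 SD to represent surgery), type I error at ρ = 0 was 4.4% for change and 4.6% for the postoperative score. With a true effect of 1.0, the mean estimates were 1.01 and 1.00. Power was 36% for change against 61% at ρ = 0, and 60% against 61% at ρ = 0.5, the same pattern as the table.

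**Within-arm test.** In the same simulation with no drug effect, the signed-rank test of baseline against the postoperative score rejected in 55% of runs at ρ = 0, 72% at ρ = 0.3 and 85% at ρ = 0.5. The +1 SD shift is an assumption, but any real shift from surgery acts the same way in both arms.

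**The case against.** A reader might infer that no patient can have a meaningful ES4 score before surgery, that surgery-specific items would be left blank and those patients lost from the change analysis, or that the baseline merely records tumour symptoms. The article supports none of these. It does not list the ES4 items or say that any apply only after surgery, and a one-line description of a scale's purpose does not show that it cannot be scored earlier. Outcomes (2.4) expressly plans assessment before as well as after surgery. The exclusion for "History of abdominal surgery (except for appendectomy or caesarean section) or ileus" adds nothing, because the baseline precedes the esophagectomy whatever a patient's earlier history.

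The stronger objection is that the randomised contrast is sound. The baseline is taken before treatment, so its expected value is the same in both arms, and the expected difference in change equals the expected difference in postoperative score. That stands. It also stands that the direction of the precision effect is unknown. With equal SDs, change loses power below ρ = 0.5 and gains above it, so simply replacing change with an unadjusted postoperative score could make matters worse.

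The planned analysis of covariance answers this only if baseline ES4 is in it and it is the main comparison, and 2.11 says neither. The within-arm problem is general to uncontrolled before/after tests and would arise with any scale affected by surgery, but 2.11 still gives that test primary status for ES4.

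**Conclusion.** The concern holds as one of precision and interpretation, not of bias. For the between-arm comparison, the loss is conditional. With equal SDs and 12 per arm, power for a 1-SD effect falls to 38% at ρ = 0 or 51% at ρ = 0.3, against 65% to 69% for the baseline-adjusted score (63% to 67% with the small-sample allowance). At ρ = 0.5 or above, change matches or beats an unadjusted postoperative score. A low correlation is plausible because a major operation separates the two readings, but it remains an assumption. The case for baseline adjustment does not depend on it, since adjustment is about as precise as change or more precise at every value checked.

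The conclusion on the within-arm test needs no assumption about ρ: a comparison that spans the esophagectomy cannot separate drug from surgery. The change is worth making, with medium confidence about how much precision is at stake.

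**What to change.** In Statistical methods (2.11), treat ES4 separately from HADS:

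- Make the main between-arm ES4 analysis an ANCOVA of the postoperative score at the end of treatment (42 days after surgery), with the preoperative ES4 score as a covariate, and report the adjusted difference with its confidence interval.
- Keep the within-arm ES4 baseline-versus-treatment comparison as a description (means and intervals by time point), not as a primary test.

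A sentence on why ES4 is scored before surgery, and what it is taken to measure then, would also help.

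This takes a sentence or two and uses scores already planned. The cost is one model degree of freedom (about 2 percentage points of power at ρ = 0, where the covariate brings nothing, once chance imbalance is counted) and a within-arm p value given up.

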### Sample size

2.6

There is no clinical evidence regarding the treatment effects of BRIHK for anxiety or water brash. Therefore, we will estimate the appropriate sample size based on feasibility instead of on statistics.

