### Recruitment

2.7

Twenty-four Participants will be recruited from outpatients in the esophagus-stomach surgery department at Tohoku University Hospital, Sendai, Japan.

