### Randomization, allocation, and blinding

2.8

Registration and allocation of the participants will be performed by the investigators and WDB Clinical Research Co., Ltd. The eligible patients will be blindly randomized to either arm P or arm A in a 1:1 ratio. The random sequence will be created using computer-generated permuted block randomization.

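### The comparison of primary-outcome changes between the two arms names the Wilcoxon signed-rank test, a paired or one-sample test that does not fit independent groups

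*Protocol article*

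**What the plan says.** Section 2.1 (Study design and setting) describes a "single-center, single blind, parallel randomized controlled trial". Section 2.8 (Randomization, allocation, and blinding) has patients "randomized to either arm P or arm A in a 1:1 ratio", using permuted blocks. No crossover or matching is described.

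Section 2.11 (Statistical methods) then sets out these tests for continuous measures:

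- **Within each arm, HADS and ES-4 at baseline against the treatment period:** signed-rank.
- **Between arms, change in HADS and ES-4:** the analysts will "compare them between the 2 groups using Wilcoxon signed rank test". An analysis of covariance adjusted for patient characteristics, with a confidence interval, follows.
- **Between arms, baseline characteristics and secondary outcomes:** for the secondary outcomes the text is "Wilcoxon rank-sum test for continuous valuables", and baseline characteristics are treated the same way.

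HADS and ES-4 are among the primary outcome measures in section 2.4 (Outcomes).

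**The concern.** Each patient contributes one change score per scale, and the scores in arm A come from different people than those in arm P. The signed-rank test ranks differences within pairs, or deviations of one sample from a fixed value. It has no form that takes two independent samples.

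An analyst following the text has two ways to make it run. One is to pair patients across arms in some arbitrary order. The other is to test the changes against zero, which asks whether patients changed over the perioperative period and not whether BRIHK differs from placebo. The first gives a p-value that the data do not determine. The second answers a different question.

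This is the first-listed randomised comparison of primary outcome measures, and the trial's stated aim is BRIHK against placebo. The primary analyses are assigned to a contract organisation, which has to work from the written plan.

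**Working it through.** The protocol gives no figure to reproduce: the size was set on feasibility ("we will estimate the appropriate sample size based on feasibility instead of on statistics"), with no effect size, SD or power. The check is therefore of the test against the design, followed by simulation.

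**Inputs from the protocol article.** Total 24 (2.7 Recruitment), allocated 1:1 (2.8), so 24 / 2 = 12 per arm if the split is exact. Significance level 5% (2.11).

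**Assumptions.** Two-sided testing, normally distributed changes, SD 1 in each arm (any scale can be standardised this way). Simulation runs: 4,000 or 5,000 per scenario.

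**1. Unequal arms.** Section 2.11 leaves out of the full analysis set patients who withdraw consent before the primary endpoint is assessed, and repeats the analyses in a per-protocol set. One exclusion gives 12 against 11. The paired calculation then cannot be carried out; standard software stops with an error because the two columns differ in length.

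**2. Equal arms, arbitrary pairing.** Twelve patients can be matched to twelve in 12! = 479,001,600 ways. One data set was simulated with arm means 1 SD apart, and 5,000 random pairings were tried:

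| Test | p-value |
|---|---|
| Rank-sum (one answer) | 0.141 |
| Signed-rank, smallest | 0.027 |
| Signed-rank, median | 0.176 |
| Signed-rank, largest | 0.569 |

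Few pairings fell below 0.05 (0.64%, that is 32 of 5,000), but they exist, so the order in which patients are listed can decide significance.

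Over repeated trials, pairing that ignores the data stays valid. If X and Y are the changes in the two arms, with means m + d and m, each paired difference X − Y has mean (m + d) − m = d, so a common shift m cancels. In simulation with d = 0 the rejection rate was about 4% to 5% whatever the shift. With d = 1 SD, power was about 56% (0.565), against about 60% (0.604) for rank-sum.

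**3. All 24 changes tested against zero.** With d = 0 the pooled sample has mean m, so the test is of m = 0. The treatment effect plays no part.

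| Shift common to both arms (SD) | Pooled signed-rank, p < 0.05 | Rank-sum, p < 0.05 |
|---|---|---|
| 0.3 | 28% | 4–5% |
| 0.5 | 62% | 4–5% |
| 0.8 | 96% | 4–5% |
| 1.0 | 99.7% | 4.5% |

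A shift common to both arms is plausible because the outcomes are measured before and after a major operation.

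**4. Consistency within section 2.11.** Signed-rank is used correctly for within-patient comparisons, and rank-sum correctly for the two other between-arm comparisons of continuous variables. Only the between-arm comparison of HADS and ES-4 departs from that pattern.

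**The case against.** The strongest reply is that this is a one-word slip with little practical consequence.

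- **The intended test is evident.** The same section uses rank-sum for the other between-arm comparisons, and software would refuse the paired test once the arms differ in size. This lowers the risk of a wrong analysis but leaves the text uncorrected. Nothing else in the article overrides it.
- **The pooled test is not what the text describes.** The sentence asks for a comparison between two groups, so the 28% to 96% figures belong to a misreading. That is fair: they show what happens under one of the two ways of running the named test and should be read conditionally. Under the other way, arbitrary pairing, the type I error stays near 5% with a small loss of power. What remains is dependence on patient order and failure with unequal arms.
- **The ANCOVA is a valid two-group method.** It is, so the plan does contain a usable randomised comparison. It comes after the signed-rank test, no precedence between the two is stated, and it does not change the named test.
- **The word primary is attached to the within-arm analysis.** Also true, and the sentence covers only HADS and ES-4, not EAT-10 or videofluoroscopy. But HADS and ES-4 are primary outcome measures, and a within-arm comparison cannot show that BRIHK differs from placebo.
- **N is small, feasibility-based, and p-values are unadjusted.** This limits how much rests on any single test. It does not justify naming one that does not fit.

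**Conclusion.** The plan is wrong as written and should be corrected before analysis. The test named for comparing HADS and ES-4 changes between arms is not a two-sample test, whatever the distribution of the data. That conclusion follows from the design alone and rests on no simulation assumption.

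The size of the consequence depends on how the analyst would resolve the mismatch: no result at all with unequal arms, a p-value dependent on ordering with equal arms, or a test of perioperative change if the data are pooled. The simulated figures assume normal changes, 12 per arm and two-sided 5% testing. The error is probably clerical, and the ANCOVA offers a sound alternative, so the harm is avoidable. Left in place, though, the choice of test would have to be made after the data are in.

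**What to change.** In section 2.11, for the inter-group analysis of change in HADS and ES-4, replace the signed-rank test with the Wilcoxon rank-sum (Mann-Whitney) test. Keep signed-rank for the within-patient comparisons with baseline. Carry the same wording into the statistical analysis plan. An acceptable alternative is to declare the ANCOVA the main between-arm analysis, with rank-sum as support.

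The rank-sum test runs with unequal arms and held its type I error at 4.3% to 4.5% in simulation at 12 per arm. The correction changes one term in the text. It does not alter the sample size, visits, data collection or anything a patient undergoes.
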